## Abstract

Background: Borderline Personality Disorder (BPD) is a debilitating mental health condition characterized by emotional dysregulation and interpersonal dysfunction, with perceived social rejection exacerbating these issues. Emerging evidence suggests that a single session of transcranial direct current stimulation (tDCS) over the right ventrolateral prefrontal cortex (rVLPFC) may decrease the unique tendency of BPD patients to feel rejected even when socially included during a laboratory task. Objectives: This protocol outlines a double-blind, sham-controlled study evaluating the longitudinal effects of repeated anodal tDCS over the right ventrolateral prefrontal cortex (rVLPFC) on rejection-related emotions (RRE) during real-life social interactions in individuals with BPD. Methods: Sixty BPD patients will be randomized to receive real or sham tDCS across 10 daily sessions, coupled with an ecological momentary assessment (EMA) protocol capturing emotional and behavioral responses to real-life social interactions over four timepoints: baseline, during treatment, ten days post-treatment, and three months post-treatment. Primary outcomes include changes in RRE, with exploratory analyses examining feelings of social connection, aggressive tendencies, trust toward others, and interpersonal and affective dynamics. Multilevel modeling will assess temporal and group-level effects. Expected Results and Impact: This study aims to establish the efficacy of tDCS in reducing BPD patients’ negative emotional response in real-life social situations and to determine whether such effects are maintained in time. The findings could advance the clinical application of tDCS as an adjunctive intervention to alleviate social–emotional impairments in BPD, addressing gaps in current treatment approaches and guiding future research into the neural mechanisms of social emotion regulation.

## 1. Introduction

Borderline Personality Disorder (BPD) is a serious, prevalent mental disorder with an adolescent onset. It is linked to high functional impairment, extensive treatment utilization, high mortality rates by suicide and other causes, and high societal costs [1]. Disturbed and instable interpersonal relationships are a core and debilitating feature of BPD [2,3]. Difficulties in systems for social processing are considered a key determinant of BPD interpersonal dysfunction [4]. Specifically, BPD patients exhibit a unique, biased view of others as rejecting them even when they are socially included by others, reporting greater negative affect following social inclusion than non-BPD groups [5]. This altered perception of social inclusion might contribute to the marked instability in close relationships in BPD, characterized by an unrealistic fear of abandonment and shifts between devaluation and idealization of others [1]. Studies using Cyberball [6], a virtual ball-tossing game simulating different levels of social inclusion, demonstrated that BPD patients, as compared to healthy controls, reported being more threatened in their need to belong and having greater rejection-related emotions not only when objectively excluded, but also when fairly included [7,8,9,10,11]. Only a laboratory condition of over-inclusion, in which participants were more than fairly included by others, was associated with a reduction in negative emotions to levels comparable to those of control participants, but not with similar degrees of social connection nor satisfaction with fundamental needs [10,12,13]. Importantly, this response pattern is not explained by an altered cognitive, objective rejection perception during the varying inclusionary conditions, which is intact in BPD [14]. Rather, BPD patients seem to exhibit a deviant emotional reactivity and affective evaluation in social scenarios, which makes them feel rejected and socially disconnected from others even during “fair”, adequate social exchanges [13,14].

In humans, actual social exclusion elicits painful feelings and activates brain regions involved in emotion regulation. Evidence suggests that the right ventrolateral prefrontal cortex (rVLPFC) may play a key role in the regulation of the negative emotional responses to social exclusion simulated by the Cyberball experiment [15,16,17,18]. Among healthy subjects, stimulating the rVLPFC using non-invasive neurostimulation techniques, such as anodal transcranial direct current stimulation (tDCS), decreases social pain and aggressive reactions following the Cyberball social exclusion condition [19,20]. Conversely, the downregulation of the same area using cathodal tDCS increases the negative emotions experienced following social exclusion [21].

Building on this evidence among non-clinical samples, we recently evaluated [14] whether, in BPD patients, a single session of anodal tDCS over the rVLPFC could reduce rejection-related emotions (RREs) following those Cyberball conditions associated with perceived social exclusion (which for those with BPD, but not healthy controls, also included fair play conditions). In a double-blind, sham-controlled, randomized pilot trial including forty patients with BPD, we found that, as compared to a sham stimulation, real anodal tDCS over rVLPFC reduced RREs during both social exclusion and fair inclusion, but not during over-inclusion. Specifically, real tDCS was effective in decreasing the levels of RREs experienced after fair inclusion to levels comparable to those experienced in the over-inclusion condition, while BPD patients receiving the sham stimulation still reported greater RREs in the inclusion condition than in the over-inclusion condition. These laboratory results suggest that, in BPD, anodal tDCS over the rVLPFC may be effective in decreasing BPD patients’ unique tendency to feel rejected even in fairly including interpersonal contexts, which is a key determinant of BPD patients’ interpersonal and psychosocial difficulties.

Overall, these findings may pave the way for further investigations on the application of tDCS over the rVLPFC as a treatment strategy in BPD. While effective psychotherapies for BPD decrease symptom severity at a clinically important level, improvements in social functioning are small and do not meet the criterion of minimal clinically relevant change [22]. In addition, medications have only modest and inconsistent effects in BPD and do not alter the course of the disorder [1]. In this context, non-invasive brain stimulation techniques may prove useful as an adjunctive to psychotherapy. Specifically, tDCS is a safe, inexpensive, well-tolerated, and easy to use device [23,24].

Previous tDCS research in BPD targeted mainly the dorsolateral PFC, showing a significant reduction in impulsivity and emotional dysregulation, although the variability in experimental procedures and outcome measures makes direct comparisons with the few existing studies difficult [25,26]. Our study [14] showed the effectiveness of anodal tDCS over rVPFC in downregulating feelings of rejection, pointing toward the rVLPFC as an alternative target to tap emotional reactivity. To our knowledge, however, no study has yet investigated whether these results, achieved during a laboratory experiment simulating varying degrees of social inclusion, might also extend to the achievement of more balanced real-life interpersonal exchanges (e.g., via a far-transfer effect).

Therefore, the present study evaluates whether repeated sessions of anodal tDCS over the rVLPFC result in long-lasting improvements in the regulation of RREs that generalize to daily interpersonal interactions for those with BPD. For this aim, BPD patients will be randomized to receive either a real or sham tDCS protocol of repeated daily stimulation for 10 working days. They will be asked to assess their daily emotional responses to real-life significant social interactions using an experience sampling of interpersonal interactions, or ecological momentary assessment (EMA) at multiple timepoints (e.g., before, during, and both 10 days and 3 months after the end of the tDCS protocol).

Based on previous evidence that among HC anodal tDCS over the rVLPFC decreases aggressive reactions following social exclusion [20], and that BPD patients feel disconnected by others even in including and over-including scenarios [10] and exhibit extensive impairments in trust processes [27], the EMA protocol will also assess participants’ momentary feelings of social connection and trust toward others, their level of aggressive tendencies, and their perception of their own and their interaction partner’s behavior.

In our prior work, we showed the utility of EMA to evaluate affective and interpersonal changes in patients with BPD treated in psychotherapy, suggesting not only that the occurrence and volatility of daily negative affects decreased over time periods but also that this was accompanied by shifts in interpersonal perceptions [28]. BPD patients (N = 45) made simple ratings of their perceptions of interpersonal warmth/dominance (i.e., is the behavior friendly or unfriendly, agentic or passive?) and affect valence/arousal (i.e., is the emotion happy or sad, intense or quiet?) in both themself and others; multilevel models examined shifts in covariations between these dimensions over the time period during an intervention. Related to the present study, over the course of treatment, BPD patients’ momentary perceptions of others as being more affectively aroused and interpersonally dominant was increasingly connected to seeing them as more friendly. Put differently, the tendency to view an interpersonal event as warm and friendly was associated with a wider range of other’s behaviors and affects, now including even those perceived to be more emotionally intense and agentic. Thus, EMA provided a powerful tool for demonstrating whether experiences of warmth/closeness were associated with highly contextual versus broad interpersonal experiences, as well as shifts in those associations over time via intervention.

Our main hypothesis is that participants receiving the actual tDCS protocol will report decreased RREs over time periods during daily interpersonal interactions (significant change T0–T1, sustained in T2) than participants receiving the sham protocol. We will also explore whether this decrease is also sustained 3 months after the end of the tDCS protocol (T3).

Furthermore, as a further exploratory aim, we will assess BPD patients’ feelings of social connection, aggressive tendencies, trust feelings, and interpersonal and affective dynamics during daily interpersonal interactions. For these exploratory aims we hypothesize that participants in the real tDCS group, as compared to participants in the sham group, will report greater feelings of social connection, lower aggressive tendencies, and higher trust toward others, and will rate their perceptions of their daily interpersonal events as increasingly warm/friendly and inclusive over time (significant change T0–T1, sustained T2–T3). We also hypothesize shifts in covariations among interpersonal/affective dimensions over time (significant change T0–T1, sustained T2–T3) such that participants perceive warmth/friendliness across a wider range of daily experiences of inclusion, affective intensity, and interpersonal dominance in the real tDCS group vs. sham.

As a last exploratory aim, we will assess the tDCS effects on BPD symptoms, reflective functioning and emotion regulation over time: specifically, we hypothesize that real tDCS will lead to an improvement in these dispositional dimensions (significant change T0–T2, sustained T2–T3).

## 2. Materials and Methods

### 2.1. Sample Recruitment

This study will involve 60 BPD patients who will be recruited among outpatients seeking treatment at an Italian community-based Department of Mental Health, after obtaining approval from the Local Ethical Authority. An a priori power analysis, performed with G-Power 3.1 [29], considering a F-ANOVA mixed repeated measures, with a between-subjects factor (tDCS group, 2 levels: sham and real tDCS) and a within-subjects factor (time, 3 levels: T0 = baseline, T1 = during the tDCS protocol, T2 = 10 days after the end of the tDCS protocol; a subsample collected T3 = 3 months after the end of the tDCS protocol were not included in the power analysis), resulted in a sample size of 30 participants (15 per group) to detect reliable outcome measures with α = 0.05, effect size (d) = 0.28, and power = 0.95. Notably, the effect size of 0.28 was based on the effect sizes of previous works from the research group [19,20,21]. We doubled the sample size suggested by the power analysis to account for the number of participants needed in the EMA protocol. While our EMA protocol was more intensive than average, a meta-analysis of response compliance in EMA studies with BPD patients showed that they were tolerant of more intensive prompt schedules and evaluation days, with a 79% compliance rate [29]. Further, we have adopted many design features associated with greater compliance in EMA studies of psychiatric patients, including regular prompt intervals spaced out over a longer period of time [30]. There are power increases as the number of observations increases in a repeated measures design; in the 30-day EMA protocol (T0-T2), participants rated approximately 150 events (5 events/day × 10-day bursts × 3 bursts) (Figure 1). We assumed an average compliance rate of 80% for all EMA prompts (120 observations per participant for T0–T2), thus accounting for missing data. Figure 1 provides a power curve for multilevel models, showing that 60 participants provided adequate power (>0.75) to detect a medium (d > 0.5) effect, assuming an 80% completion rate during T0-T2 with an ICC value of 40%, as per our prior studies [28,31,32,33]. The subsample of participants who agreed to complete a 3-month follow up (we expected 50% of the original sample), assuming a compliance rate of 80% for all EMA prompts, resulted in an additional 40 observations per subsample participant at T3.

All participants were first evaluated by a trained investigator (senior-level resident in psychiatry) during an individual diagnostic screening to determine their eligibility for the study. Further, information on socio-demographic features, personality features (see Trait measures below), and ongoing pharmacological treatments was collected. Only patients meeting the inclusion criteria and not having any exclusion criteria for study participation were enrolled in the study. The inclusion criteria for both groups was a BPD diagnosis according to DSM-5 [35] criteria, as established by the Structured Clinical Interview for DSM-5 PD (SCID-5-PD) [36], and age 18–65. The exclusion criteria were as follows: a diagnosis of psychosis, active substance dependence, or an active mood disorder, as established by the Structured Clinical Interview for DSM-5, Clinician version (SCID-5-CV) [37]; cognitive impairment (based on clinical judgment); tDCS exclusion criteria, such as unstable medical conditions or the diagnosis of neurologic or heart diseases; presence of metallic implants, pacemakers, or acoustic prostheses; and some specific drug treatments, mainly tricyclic antidepressant therapies [25]. After the screening and the baseline assessment, all participants were then trained on the use of the app for the EMA and on the use of the experimental measures implemented in the protocol (see Section 2.3. *EMA protocol*).

### 2.2. Trait Measures

Patients will be individually administered the following questionnaires to evaluate their symptoms and their dispositional ability to deal with rejection issues and emotion regulation:

Difficulties in Emotion Regulation Scale (DERS) [38], a 36-item self-report questionnaire (Likert scale, 1–5) designed to assess multiple aspects of emotional dysregulation. DERS subscales investigate the non-acceptance of emotional responses, difficulties engaging in goal-directed behavior, impulse control difficulties, lack of emotional awareness, limited access to emotion regulation strategies, and a lack of emotional clarity.

Adult Rejection Sensitivity Questionnaire (A-RSQ) [39], a self-report questionnaire that presents respondents with 9 potential rejection situations. For each scenario, participants indicate on a 6-point Likert scale their level of expectation of rejection and of anxiety about rejection. For the current study, we added a third question about participants’ anger about rejection [40,41], leading to three different subscales: expectations of rejection, anxiety about rejection, and anger about rejection [42].

Reflective Functioning Questionnaire (RFQ) [43,44], a self-report, 8-item questionnaire (Likert scale, 1–7) assessing reflective functioning. The RFQ has two subscales, each containing 6 items, assessing certainty and uncertainty about the mental state of oneself and others.

Borderline subscale of the Personality Assessment Inventory (PAI-BOR) [45], a 24-item, widely known, and reliable measure (Likert scale, 1–4) for borderline features, such as affective instability, identity problems, negative relationships, and self-harm.

All these questionnaires are well-validated measures that are extensively employed in BPD populations to evaluate their specific difficulties in emotion regulation, rejection issues, reflective functioning, and symptoms.

Patients will complete again the above-mentioned questionnaires at T2 and at T3, to explore whether anodal tDCS over the rVLPFC might lead to potential changes in these dispositional measures as well.

### 2.3. EMA Protocol

To measure the emotional and behavioral response stemming from participants’ everyday social relations, participants, after being trained on the use of an app on their smartphones, will undergo an EMA protocol in four different assessment periods, each lasting 10 days (Figure 2). The specific details are as follows:

T0: starting 10 days before the tDCS protocol to assess the baseline behavioral and emotional responses to social relations;

T1: during the 10 days of the tDCS protocol, in order to assess the effects of tDCS during the protocol;

T2: 10 days after the end of the tDCS protocol, to assess if the potential effects persist even after the end of the tDCS protocol.

T3: 12 weeks following the end of the tDCS protocol for 10 days, to assess if the potential effects persist in the long-term after the end of the tDCS protocol.

For each day of the EMA protocol, participants will receive five prompts from an app on their smartphones at five different times of the day: two in the morning (around 9 to 12.30 pm), two in the afternoon (around 15 to 19 pm), and lastly, one in the evening (around 20 to 22 pm), asking them to assess the last significant social encounter of the day (lasting at least 5 min). Moreover, participants will be asked to spontaneously report their reactions immediately after any significant social encounter (lasting at least 5 min) at least three times/day. The average EMA survey completion time in our prior study [28] was 2 min 43 s, or about 15 min per day.

For both signal-initiated and event-initiated EMAs, participants will be directed to an online survey that will ask respondents to fill in the following measures:

Primary Outcome Measure: Rejection-related emotions. Assessed by the Rejected Emotions Scale [46]. Participants will rate how they felt during *Cyberball* on a number of adjectives measuring six emotions: anger, happiness, hurt, rejection feelings, anxiety, and sadness. These ratings will be made on a 7-point scale ranging from “not at all” to “extremely”. For the sake of compliance and brevity, the original scale, assessing the different dimensions with 4 items each, has been shortened to a single item assessing the singular dimensions, for a total of 6 items.

Exploratory outcome measures:

Interpersonal and Affect Assessments.

Patients will make event-contingent recordings following any interpersonal interaction lasting 5 min or longer. Ratings include their own interpersonal behavior (self-agency, self-communion) as well as their perception of their interaction partner’s interpersonal behavior (other-agency, other-communion). Higher scores indicate greater perceived dominance (from unassured–submissive to assured–dominant) and communion (from cold–quarrelsome to warm–agreeable). Patients will also rate their own affect (self-activation, self-valence) as well as their perception of their interaction partner’s affect (other-activation, other-valence). Higher scores indicate higher perceived activation (from quiet–passive to active–energized) and higher perceived valence (from sad–upset to happy–pleased).

Social connection. Assessed by the Inclusion of Other in the Self scale (IOS) [47], a single-item, pictorial measure of the psychological overlap between the self and the other. Higher scores indicate a higher degree of social connection. Participants will rate their impression of closeness with the other person during the interpersonal event by choosing among 7 images. Each image shows two diagrams, the former related to “yourself”, the latter related to “the other”, which can be completely separated (“A”) up to partially overlapped (“G”).

Trust will be assessed by asking the participants “In this social interaction, how much did you trust the other person?”. This measure will be scored on a 7-point scale ranging from “not at all” to “extremely”.

Aggressive temptations. Assessed by the Aggressive Temptation Scale—short version (ATS) [48], a 6-item questionnaire (1–7 Likert scale) measuring participants’ self-reported temptation to engage in aggressive behaviors (e.g., humiliating another person or ignoring another person). Particularly, participants will be reminded that this scale will not ask whether they would have performed each behavior, but rather the degree to which they would have been tempted to do each one during the interpersonal event they are rating.

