### 2.4. Transcranial Direct Current Stimulation (tDCS) Protocol

Participants will be randomly assigned to two stimulation conditions: anodal (real) or sham tDCS over the rVLPFC. The tDCS treatment, either real or sham, will last 10 working days and comprise 20 min daily sessions. The stimulation will be applied at an intensity of 1.5 mA, with electrodes of 25 cm^2^ (anode, current density of 0.06 mA/cm^2^) and 35 cm^2^ (cathode, current density 0.042 mA/cm^2^) in line with the safety standards of tDCS [24]. We opt for differently sized electrodes to increase the focality of the stimulation [24]. In the sham modality, all the stimulation parameters (electrode sizes and montage, current intensity, number of sessions) will be kept identical, except for the stimulation duration, which will last only 20 s, with 30 s of rump-in/out as in the real condition to maintain the same physical sensations, thus keeping the participants blind to the tDCS condition [24,49]. An intracephalic montage will be adopted, with the anode placed over the rVLPFC, while the cathode will be placed on the contralateral supraorbital region.

We opt for an intracephalic montage based on prior research on tDCS clinical use [50,51], and to maintain consistency with the montage and tDCS parameters that effectively reduced pain-related emotions in our previous work [19,20,52]. The same electrode positioning procedure, based in the EEG 10-20 system of our previous studies [19,20,52], will be employed. Specifically, the anode will be positioned over F6 (MNI coordinates: 58, 30, 8), which corresponds to the rVLPFC. The effectiveness of such a montage to target the rVLPFC has been tested employing the free software COMETS v.1.04 (http://www.COMETStool.com, accessed on 15 March 2025) [53] to run a computational model of the current flow (figure below taken from Riva et al., 2017 [52]). This model showed that the strongest electric field was concentrated around the cortical area beneath the target electrode (Figure 3).

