tDCS will be delivered during the *Cyberball* paradigm, a virtual ball-tossing game that reproduces different levels of social inclusion by manipulating the percentage of tosses that participants receive from two other computer-controlled co-players. After about five minutes of stimulation, participants will play first the social inclusion (33% of throws received), then the social exclusion (10% of throws), then the over-inclusion (45% of throws) conditions of the game. The order of these experimental phases is fixed, ensuring that the game ends with the over-inclusion condition, which is typically not associated with negative emotions in BPD [10,13], for ethical reasons. The choice in the study design to deliver tDCS during the *Cyberball* stimulation design is based on recent evidence on the state-dependency of tDCS, pointing to the opportunity to timelock the stimulation to a concurrent activity involving the stimulated target area in order to achieve specific effects [54,55,56]. tDCS experiments will be conducted by trained investigators and participants can stop the stimulation at any time if they want to. TDCS is not invasive, with few adverse effects, mostly consisting of an itching sensation during the ramp-in phase of the current [57]. At the end of the tDCS treatment, participants will complete a questionnaire to investigate the eventual side effects and to control for tDCS blinding effectiveness [58]. Checking blindness effectiveness indeed becomes more crucial when multiple sessions are included in a protocol. In particular, the questionnaire [58] explores participants’ beliefs on tDCS condition assignment. The frequency of correct vs. incorrect guesses will then be compared between the real vs. sham control group by means of a Chi-square test.

All subjects will be extensively debriefed upon completion of the study. They will receive detailed information about the tDCS protocol and its purpose and will have the opportunity to have their data deleted should they so wish.

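### The EMA event rules do not separate the daily study session from everyday encounters, so T1 ratings, and the T0–T1 contrast, may mix laboratory and real-life responses

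*Protocol article*

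**What the plan says.** Section 2.3 (EMA Protocol) gives three descriptions of what a patient should rate.

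- Signal prompts, five a day: "asking them to assess the last significant social encounter of the day (lasting at least 5 min").
- Self-initiated reports: patients are to "spontaneously report their reactions immediately after any significant social encounter (lasting at least 5 min) at least three times/day".
- Under the interpersonal and affect measures the rule is wider and drops the word significant: "Patients will make event-contingent recordings following any interpersonal interaction lasting 5 min or longer".

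The same section places one of the four bursts inside the treatment period: "T1: during the 10 days of the tDCS protocol, in order to assess the effects of tDCS during the protocol". Section 2.4 says of the treatment, real or sham, that it "will last 10 working days and comprise 20 min daily sessions". Trained investigators run the sessions. During stimulation the patient plays Cyberball, which varies social inclusion by "manipulating the percentage of tosses that participants receive from two other computer-controlled co-players".

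The purpose is stated clearly. The Introduction asks whether the laboratory findings "might also extend to the achievement of more balanced real-life interpersonal exchanges (e.g., via a far-transfer effect"), and section 2.3 opens by naming patients' ordinary social life as the target. The survey items listed there cover rejection-related emotions (RRE), own and partner behaviour and affect, closeness, trust and aggressive temptation. None asks who the partner was or where the encounter took place.

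**The concern.** The trial asks whether a laboratory effect carries over to daily life. The main hypothesis (Introduction) is a larger fall in RRE from T0 to T1 with real than with sham tDCS, sustained at T2. T1 is also the only burst in which patients attend a session on each working day, and a session with an investigator can satisfy the written event rules. A prompt answered after the session, with no other notable encounter in between, would lead the patient to it. The requirement of at least three self-initiated reports a day adds a further reason to use it.

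The pilot described in the Introduction found lower RRE with real than with sham stimulation in two of the three Cyberball conditions. If T1 ratings include session experiences, a response arising in the laboratory could be counted in the contrast meant to show transfer out of it. The mix of encounter types would also differ between T1 and the other bursts.

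**Working it through.** **1. The plan's own counts (section 2.1).** Prompts over T0–T2: 5 per day × 10 days × 3 bursts = 150, as stated. At 80% compliance: 150 × 0.80 = 120, as stated. Per burst this is 50 planned and 40 answered prompts.

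**2. Does the session meet the event rule?** The criteria are a social encounter or interpersonal interaction, a duration of at least 5 minutes and, in two of the three descriptions, significance.

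- *Contact with the investigator.* The session lasts 20 minutes. If the contact itself lasts 5 minutes or more, it meets the wider rule outright. Under the other two it depends on whether the patient finds it significant.
- *The Cyberball game.* This is less clear. The co-players are computer-controlled, while the closeness, trust and partner-behaviour items presuppose another person.

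**3. In which bursts?** T1 overlaps the sessions. T0 precedes them, and T2 and T3 follow them. Questionnaires repeated at T2 and T3 (section 2.2) may bring occasional staff contact, but no daily session.

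**4. Largest share of T1 ratings, assuming one session report per session day.** If all 10 burst days are session days, there are 10 such reports. If the burst is 10 consecutive calendar days, it holds 6 to 8 working days, so 6 to 8 reports.

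| Session days in T1 | Of 50 planned prompts | Of 40 answered prompts | Of 80 reports (5 prompts + 3 self-initiated per day) |
|---|---|---|---|
| 6 | 12% | 15% | 7.5% |
| 8 | 16% | 20% | 10% |
| 10 | 20% | 25% | 12.5% |

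The answered-prompt column assumes that every session-related prompt is among those answered. Two session reports per session day would double the last column to 15–25%.

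**5. Effect on the contrast.** Let p be the share of T1 ratings that describe the session. Then

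observed T1 arm difference = (1 − p) × real-life difference + p × session difference.

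The document gives neither p nor the session difference on the EMA scale, so the values below are assumptions, with p = 0.20:

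- real-life 0, session 0.5 SD: 0.80 × 0 + 0.20 × 0.5 = 0.10 SD (apparent effect without transfer)
- real-life 0.5 SD, session 0: 0.80 × 0.5 + 0.20 × 0 = 0.40 SD (diluted)
- real-life 0.5 SD, session 1.0 SD: 0.80 × 0.5 + 0.20 × 1.0 = 0.60 SD (inflated)

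On the 7-point scale, an assumed 1-point session difference with no real-life effect gives 0.20 × 1 = 0.2 points. At p = 0 the observed difference equals the real-life difference.

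**The case against.** The strongest reply is that this rests on silence in a condensed article. Patients are trained on the app and the measures (sections 2.1 and 2.3). The training content and full item list may sit in a document not shown, and the stated target of everyday relations, together with the word significant, may steer patients away from reporting the session. This stands as a limit on size: the true share could be near zero. It does not remove the point. The event rules are written out, in more than one form, and as written they admit the session. A stated purpose is not an exclusion rule.

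The mechanism is also weaker than it first looks. Both arms attend the same sessions, so the presence of session ratings is balanced and only a difference in their content can bias the contrast. The pilot found no arm difference in over-inclusion, and section 2.4 fixes the order so that every session ends there. No arm difference in feelings towards study staff is reported anywhere. The hypothesis further requires the change to be sustained at T2, so an artefact confined to T1 would not produce the full predicted pattern. All of this stands.

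A reader might infer that session reports could never be removed afterwards. That goes too far: with session and prompt times, prompts close to a session can be set aside approximately. What is lacking among the listed items is a direct identifier.

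**Conclusion.** The point holds in a limited form. The written event rules do not separate the study session, chiefly investigator contact and possibly the game, from everyday encounters. Because such reports can arise daily only in T1, the T0–T1 arm contrast may not measure daily life alone.

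The upper-bound shares assume one session report on every session day; the true share is unknown. The direction of any distortion is open as well. The effect sizes used above are illustrations, not estimates.

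A reader might infer that a T1 benefit would simply be the known laboratory effect relabelled. The documents do not support that. They give no number of session reports and no laboratory effect on this scale, and the order of game conditions and the T2 requirement both work against it. The T2 and T3 contrasts are not affected by the daily sessions. The change is still worth making, because the affected contrast belongs to the main hypothesis and the remedy is small.

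**What to change.** 1. State at EMA training and in the survey header that study sessions, the Cyberball game and contacts with study staff are not eligible events in any burst.
2. Add one tick item for the partner or setting (for example partner, family, friend, colleague, clinician, study staff).
3. Exclude study-staff reports from the RRE outcome in all bursts.
4. Add a T1 sensitivity analysis that leaves out prompts falling on the same half-day as a session.

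The cost is one instruction, one extra item per survey and one additional analysis, with slightly fewer usable T1 reports.
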